**Fig. 2 Fig2:**
[figure not shown]
Outcome measures

The Multidimensional Fatigue Inventory questionnaire (MFI20) consists of 20 questions grouped in five dimensions and scored from 1 to 5. The Hospital Anxiety and Depression Scale (HADS) is a self-rated scale measuring anxiety and depression in hospital and in the community. The Euroqol-5D (EQ-5D) health questionnaire is a standardized instrument, which divides health status into five dimensions. The EQ-5 questionnaire is validated in hemiplegic and stroke patients [28, 29]. The Modifiable Activity Questionnaire (MAQ) evaluates the perception of PA through a listing of all activities done during the last 6 months. The Barthel index is a scale evaluating the dependence and independence of patients where a score of 0 represents total dependence and 100 represents complete independence. The Functional Ambulation Classification (FAC) classifies ambulation from 0 (nonfunctional ambulation) to 8 (independent ambulation). Lower limb strength will be measured three times per leg using the Dynatrac2 (Ysy medical). Finally, the heart rate variability test will be carried out in the resting and standing position according to the tilt-test protocol [30].

### Participant timeline

The Ticaa´dom protocol will start after the participant has signed the written informed consent form during the first clinical examination. Each patient will be evaluated in a specific order presented following the SPIRIT recommendations for interventional trials (Fig. 3).

**Fig. 3 Fig3:**
[figure not shown]
Participant timeline. *FAC* Functional Ambulation Classification, *HADS* Hospital Anxiety and Depression Scale, *6MWT* Six Minute Walk Test, *MFI* Multidimensional Fatigue Inventory questionnaire, *EQ-5D* Euroqol-5DHealth status questionnaire, *MAQ* Modifiable Activity questionnaire, *HCCQ* Modified Health Care Climate questionnaire

### Sample size calculation

The Biostatistics unit of the Limoges University has calculated the sample size using the Nquery Advisor software (Version 6.1). The calculation is based on previous studies according to the protocol similarities in the home-based setting and protocol outcomes [31]. We hypothesized that the PA incentive program would improve the 6MWT distance by 30%. We have performed bilateral estimation with variance of 30%, alpha risk of 5% and power of 80%. The resulting required sample size was 36 subjects per group. We added 15% to ensure the statistical power of the study. As a result, the total sample will be 84 patients: 42 in the HB-PAI and 42 in the CG group (Fig. 4).

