### Outcomes

Outcome assessments will be performed after hospital discharge (T0), at 6 months (T1), and at 12 months (T2). The PA therapist will confirm the T1 and T2 medical appointments 3 weeks before the due date to avoid time bias. If the participant cannot attend the medical appointment, it will be delayed for a maximum of 3 days. The same practitioners, a medical doctor and a professional PA therapist will perform all assessments at the University Hospital of Limoges. The clinical examination, test and questionnaires will last around 90 min.

The primary outcome will be the distance walked during the 6MWT, which is widely used in stroke studies [23, 24]. The 6MWT provides an objective measure of functional ability, endurance, and walking ability in people with physical impairments and stroke sequelae [25]. In addition, the 6MWT is a predictor of individual community walking activity, ambulation, and social integration in stroke survivors [26]. Patients will refrain from alcohol, tobacco, and caffeine consumption in the 24 hours before testing. The final score will be the distance walked during the 6MWT, and the rating of perceived exertion, assessed with the modified CR10 Borg scale from 0 to 10, will also be noted at the end of the test [27]. Secondary outcomes with the specific measurements are presented in Fig. 2.

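### The sample size of 36 per group does not follow from the stated inputs (30% improvement, "variance" of 30%, two-sided 5%, 80% power)

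*Protocol article*

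**What the plan says.** Under Outcomes, the protocol article names a continuous primary endpoint: "The primary outcome will be the distance walked during the 6MWT". Under Sample size calculation it gives the planning effect, "We hypothesized that the PA incentive program would improve the 6MWT distance by 30" per cent, and then the remaining inputs: "We have performed bilateral estimation with variance of 30%, alpha risk of 5% and power of 80" per cent. Its result is "The resulting required sample size was 36 subjects per group". A margin follows, "We added 15% to ensure the statistical power of the study", and the final figure is given as "the total sample will be 84 patients: 42 in the HB-PAI and 42 in the CG group".

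The article gives no walking distance in metres and does not say what either percentage is a percentage of.

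**The concern.** For two equal groups compared on a mean, effect, variability, significance level and power together fix the sample size. The article states all four and a sample size, and the five do not fit. This goes beyond the brevity normal in an article: figures are given, and they contradict one another.

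This paragraph is the only place where the reader learns what difference the trial was built to detect. If the result is null, one reading says the trial was about twice as large as needed for a 30% effect. The other says it never had its stated 80% power for that effect.

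**Working it through.** **Inputs** (all from Sample size calculation): effect 30%; "variance" 30%; two-sided 5%; power 80%; two equal groups; stated result 36 per group; 15% added; 42 per group, 84 in total. Assumption: both percentages refer to the same mean.

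**Formula.** With standardised effect *d* = difference / SD, the normal approximation is

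n per group = 2 × (z₀.₉₇₅ + z₀.₈₀)² / d² = 2 × (1.960 + 0.842)² / d² ≈ 15.70 / d².

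Each result was also computed exactly, with the noncentral t distribution for a two-sample t test.

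**The step that reproduces.** 36 × 1.15 = 41.4, rounded up to 42; 2 × 42 = 84. The margin and the total follow from 36.

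**The step that does not.**

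| Reading of the 30% | SD | d | n, normal approx. | n, exact t | Power at 36 | Power at 42 |
|---|---|---|---|---|---|---|
| It is the SD | 0.30 | 0.30/0.30 = 1.000 | 15.70/1 = 15.7 → 16 | 17 | 98.7% | 99.5% |
| It is the variance | √0.30 = 0.548 | 0.30/0.548 = 0.548 | 15.70/0.30 = 52.3 → 53 | 54 | 63.0% | 69.9% |

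**What 36 per group corresponds to.** Solving the formula for *d* at n = 36 gives √(15.70/36) = 0.660; the exact calculation gives 0.670. In the plan's units:

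- with SD 30%, the detectable difference is 0.670 × 30% = 20.1%;
- for a difference of 30%, the SD must be 30% / 0.670 = 44.8%;
- with a literal variance of 0.30, the detectable difference is 0.670 × 54.8% = 36.7%.

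The rounded pairs (20% with SD 30%; 30% with SD 45%) both have d = 0.667. The normal approximation then gives 15.70/0.444 = 35.3 → 36; the exact method gives 37, with 79.7% power at 36. The article states neither pair.

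**Other readings that keep two-sided 5% and 80% power:**

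- SD equal to 30% of each arm's own mean (0.30 and 0.39): 23 per group; SD 0.39 in both arms: 28.
- Log scale with a 30% coefficient of variation: 20 to 21.
- A usual allowance for the Mann–Whitney test: 18 to 20 (SD reading) or 57 to 63 (variance reading).
- A paired t test: 10 or 29.
- A change score with no correlation between the two walks (SD 0.30 × √2 = 0.424): 32 to 33. With a correlation of 0.5 this falls to 16.
- That uncorrelated change score plus a Mann–Whitney allowance: 35 to 38.

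Only the last comes near 36. It needs two ingredients that the sample size paragraph does not mention.

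**The case against.** The strongest reply is that the figure may be sound and only its description compressed. The article does not say what the percentages refer to, whether a final distance or a change was planned, or which test was entered in the software. The software output and the cited source are not at hand. An uncorrelated change score with a Mann–Whitney allowance gives 35 to 38 per group, which brackets 36, and the Mann–Whitney test is named under Statistical analysis. This shows that an error in the original calculation is not proven. It does not rescue the paragraph: neither ingredient is stated there, Outcomes defines the score as the distance walked, and zero correlation between two walks by the same patient is implausible.

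Second, the impact has no direction. "Variance" used loosely for SD is at least as natural as the literal reading, and then the trial has ample power for its stated effect. This stands: the 63% and 70% figures must not be presented as the trial's power.

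Third, correcting the text changes no patient, outcome or test, and the final confidence interval will show which effects a null result excludes. That is true. It limits the cost of the correction, but the published justification remains wrong.

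Fourth, an effect worked back from the sample size should not be presented as the original target. This also stands, and the fix allows for it.

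**Conclusion.** The concern holds. Under neither plain reading can a 30% effect, a "variance" of 30%, 80% power at two-sided 5% and 36 per group all be true. The stated inputs call for 17 or 54 per group; power at 36 is 98.7% or 63.0%, not 80%. What 36 evaluable patients per group do provide is 80% power for a between-group difference of about 0.67 SD.

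The article cannot settle which figure is wrong: effect, variability, power or sample size. The finding therefore does not show that the trial is too small. It rests on a two-sample comparison of means with equal groups, and on both percentages sharing one base, which the article does not state.

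**What to change.** Keep the total at 84. Retrieve the nQuery input and rewrite the paragraph with the figures actually entered: control-group mean distance, SD in the same unit, between-group difference, time point and test. If an SD was entered, replace "variance" by "standard deviation".

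If the input cannot be recovered, say so and give a statement of what the size provides, labelled as worked back from it and not as the original planning assumption. For example: *36 evaluable patients per group give 80% power at two-sided 5% to detect a between-group difference of 0.67 SD (about 20% if the SD is 30%; about 30% if the SD is 45%).* The percentages are rounded; taken exactly, they give 79.7% power.

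The cost is one reworded paragraph and no extra patients. The stated power or detectable effect may then differ from the published one. Trial status reports 50 of 84 enrolled, so the correction can still be made before results are known.

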**Fig. 4 Fig4:**
[figure not shown]
Patient flow chart

### Randomization and allocation

Eligible patients who agree to participate will be asked to give their written informed consent, and will then be randomized into the HB-PAI group or CG. We will randomize the patients at the first clinical examination. The randomization process will be ensured using a secure internet connection with access by individual user ID and password and encrypted data transmission to the randomization platform of the Clinical Research Unit of the Limoges University Hospital. Only the study methodologist will complete and keep the randomization list on a secure server. This randomization list will be balanced by blocks of variable size and will not include a stratification factor. All actions carried out on this platform and the identity of the person who made the changes will be automatically archived by audit trail procedure. As soon as a patient is randomized, an email will automatically be sent to all organizers of the study, i.e. the Clinical Research Assistant, Data Manager and Principal Investigator. No strategy was provided for preventing a potential imbalance between intervention and control group allocation.

### Blinding

The study will be partially blinded. Evaluation of all outcome criteria by a physical activity specialist dedicated to this matter will be performed blinded. A double-blind design is not possible for this study due to the methodology.

### Data collection, management, and analysis

A case report form (CRF) will be used to record all data, including physical activity variables and an explanation will be required for each missing piece of data. The PA therapist will collect, stock, and transcribe data clearly and legibly to the CRF.

The Biostatistics unit of the Limoges Hospital Center (CEBIMER) will create the database through the CAPTURE SYSTEM provided by CLINSIGHT Corporation. More specifically, they will adopt the “CS-DESIGNER” software to manage clinical databases using the ORACLE database.

The design and appearance of the database will be identical to the CRF. The data will be saved in real time and archived daily on a magnetic tape. The data history will be viewed through the AuditTrail system according to the computer security standards.

The Biostatistics unit will carry out consistency tests using the CAPTURE SYSTEM with a list of verification data registered on the QUERYS documentation. The investigators will check any correction made in the database twice to avoid bias before validating the database, preventing all further modifications of this version. The investigators will then export the database files in SAS format and send the tables back for statistical analysis. We will analyze the primary and secondary outcomes 6 months after final data monitoring and auditing.

### Statistical analysis

We will describe quantitative variables as mean ± standard deviation, and qualitative variables as numbers, percentages and 95% confidence intervals. We will present the study flow diagram and the patient characteristics for each group. The scientific council and the Biostatistics clinical research department will elaborate a detailed statistical analysis plan.

The analysts will compare the 6MWT distance between each group using either the matched Student’s *t* test or non-parametric Mann–Whitney test, depending on whether the data follow a normal distribution. They will also compare the qualitative variables using Pearson’s chi-squared test or Fisher’s exact test. We will compare the distributions of quantitative variables using Student’s *t* test or non-parametric Man-Whitney test.

The analysts will calculate the univariate Spearman coefficient for correlation between two quantitative variables. They will also compare data between T0, T1 and T2 in both groups using the Friedman test and Wilcoxon matched pairs test. Multivariate linear regression analysis may be performed, taking prognostic factors into account.

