### Study design and settings

Ticaa’dom is a comparative prospective, observer-blinded, monocentric, parallel, randomized controlled clinical trial. The Neurological and Physical Medicine and Rehabilitation Services of Limoges University will conduct this study in the Limousin region of France.

Ticaa’dom will also include a home-based 12-month post-discharge study conducted by professional PA therapists. The protocol will include two groups: the home-based physical activity incentive group (HB-PAI) and the control group (CG). The HB-PAI will include a physical activity incentive and education program for the first 6 months, followed by 6 months of traditional follow up. The CG will receive traditional follow up for 12 months (Fig. 1).

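### The primary between-group test is named as a matched t test, but the parallel design has no pairs; the choice of test also rests on observed normality

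*Protocol article*

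**What the plan says.** All references are to the protocol article.

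- **Outcomes:** "The primary outcome will be the distance walked during the 6MWT", with assessments at T0, T1 (6 months) and T2 (12 months).
- **Statistical analysis, primary comparison:** "The analysts will compare the 6MWT distance between each group using either the matched". The last word qualifies Student's t test. The alternative offered is Mann–Whitney, and the choice between the two is made "depending on whether the data follow a normal distribution".
- **Statistical analysis, other quantitative variables:** the same two tests are named again, this time without the word matched.
- **Statistical analysis, change over time:** "They will also compare data between T0, T1 and T2 in both groups using the Friedman test and Wilcoxon matched pairs test".
- **Study design and settings:** the trial is a "comparative prospective, observer-blinded, monocentric, parallel, randomized controlled clinical trial".
- **Randomization and allocation:** "This randomization list will be balanced by blocks of variable size and will not include a stratification factor".

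The Statistical analysis section also announces a detailed statistical analysis plan, which is not available here, and says that multivariate linear regression with prognostic factors may be performed.

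**The concern.** A matched t test works on the differences within defined pairs. Here each patient is allocated individually to one of two arms, and no section forms pairs across arms. The parametric branch of the primary analysis therefore has no data structure to act on. The non-parametric branch of the same sentence assumes two independent samples, so the two branches do not describe the same data.

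An analyst who took the sentence literally would have to invent pairs. The result would then depend on an arbitrary ordering of patients, and whenever the arms have unequal numbers of completers, the surplus patients in the larger arm would drop out of the primary test.

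A smaller concern is the selection rule. A t test comes with a mean difference, Mann–Whitney with a shift in ranks. If observed normality decides between them, the measure that carries the primary conclusion is not fixed until the outcome has been seen. The sample-size section speaks of a percentage improvement in distance, which fits a difference in means.

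**Working it through.** **1. Is there anything to pair on?** Study design and settings gives parallel groups. Randomization and allocation gives variable-size blocks with no stratification factor, and blocks do not define pairs. Within-patient comparisons over T0, T1 and T2 have their own sentence and their own tests. So no pairing is defined for the between-group comparison.

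**2. Which effect size to use?** The article gives 36 per group, a 30% improvement, a variance of 30%, two-sided alpha of 5% and 80% power. With n = 2(1.96 + 0.8416)² / d² = 15.70 / d²:

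- SD 30% (d = 0.30/0.30 = 1): n = 15.7, so 16.
- Variance 0.30 (SD = √0.30 = 0.548, d = 0.548): n = 52.3, so 53.
- n = 36 needs d of about 0.667: 15.70 / 0.445 = 35.3, so 36.

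The stated inputs do not reproduce 36 on either reading. That is a separate matter. For the present point, 0.667 SD is an **assumption** back-solved from n = 36, and 0.548 is shown beside it.

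**3. Cost of arbitrary pairing, equal arms.** For unrelated patients the variance of a paired difference is 2σ². The noncentrality is then d√(n/2), the same as for the independent test. Only the degrees of freedom change, from 2n − 2 = 70 to n − 1 = 35, and the two-sided critical value rises from 1.994 to 2.030. Exact noncentral t results with 36 per arm:

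| Assumed d | Independent t | Arbitrarily paired t | Loss |
|---|---|---|---|
| 0.667 | 0.797 | 0.786 | 0.011 |
| 0.548 | 0.630 | 0.618 | 0.012 |

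Type I error is 0.05 for both tests.

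**4. Cost with unequal arms.** The independent test has noncentrality d / √(1/n₁ + 1/n₂) on n₁ + n₂ − 2 degrees of freedom. The paired test keeps only min(n₁, n₂) pairs. The completer splits are **assumed**; the article plans 42 and 42 and gives no expected split. At d = 0.667:

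| Completers | Independent: noncentrality, power | Paired: pairs, noncentrality, power |
|---|---|---|
| 40/32 | 2.812, 0.792 | 32, 2.668, 0.734 |
| 42/30 | 2.790, 0.786 | 30, 2.583, 0.704 |

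**5. Dependence on the pairing.** In 40,000 simulated trials with 36 normal outcomes per arm, each trial was tested under two arbitrary pairings of the same data. The significance decisions disagreed in 5.6% of trials at d = 0.667, in 7.3% at d = 0.548, and in about 2% with no effect.

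**6. The normality rule.** The article names no normality criterion, so a Shapiro–Wilk test at 5% in each arm was assumed, followed by an independent t test or Mann–Whitney (8,000 simulated trials, 36 per arm). Type I error was 0.049 with normal data and 0.044 with lognormal data (log-scale SD 0.5). Neither is inflated.

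**The case against.** The strongest reply is that this is a one-word slip. The sentence says the comparison is between groups, pairs it with an independent-samples test, and is soon followed by the same two tests without the word. No pairing variable exists, so a competent statistician would run the unpaired form. That is probably what would happen. It does not dispose of the point, because the wrong word stands in the primary analysis and nothing in the article withdraws it. A later analysis plan would have to contradict the sentence rather than add detail to it.

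A reader might infer more: that the test would be run as T0 against T1 within the intervention arm, so that spontaneous recovery after stroke is credited to the programme. The article does not support this. The sentence concerns a comparison between the groups, and comparisons over T0, T1 and T2 are assigned to the Friedman and Wilcoxon tests. False-positive rates for a within-arm test would describe an analysis that is not named as primary.

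A reader might also call the between-group test invalid in the sense of an inflated error rate. That does not follow either: pairs formed without regard to outcome keep the 5% level.

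On the normality rule, the objection that it is announced in advance, that a criterion would usually sit in the analysis plan, and that no inflation was found is fair. What survives is that the effect measure depends on the data.

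**Conclusion.** Wrong as written, and of moderate severity. The named parametric primary test does not fit a parallel trial without pairs, and it is inconsistent with the alternative named beside it.

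The damage if it were followed literally is limited: about 1 percentage point of power with 36 completers per arm, about 6 points at 40/32 and about 8 at 42/30, plus a significance decision that turns on the arbitrary pairing in roughly 6–7% of trials. The power figures for unequal arms rest on the assumed 0.667 SD effect and the assumed splits; neither is stated in the article. The data-driven choice between t test and Mann–Whitney is a secondary weakness in what the trial will report, with no demonstrated effect on the error rate.

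**What to change.** Delete the word matched from the primary-analysis sentence, and fix one analysis for independent groups in advance, whatever the distribution looks like. The recommended form is a linear model of 6MWT distance on randomised group, adjusted for T0 distance, reported as a mean difference in metres with a 95% CI. The sentence should name the visit to which the model applies. Mann–Whitney can stay as a named sensitivity analysis. Deleting the word alone removes the contradiction; adjusting for T0 goes a step further, but uses a measurement already collected.

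The cost is one sentence in the protocol and a check that the analysis plan agrees with it. Sample size, visits and data collection are unaffected. The article reports 50 of 84 patients enrolled, so the correction could be made before any analysis.

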On the subject of home-based PA in the subacute phase of stroke recovery, Studenski et al. [20] compared the motor control, balance, endurance and mobility of the upper and lower extremities following a 12-week cycle ergometer program. Compared to usual care, the intervention brought about better gains (*P* = 0.0056), in the form of improved scores in the Barthel Index (BI) and Balance Berg Scale (BBS), better peak aerobic capacity, improvements in the up-and-go test (TUG) and 6MWT, and better physical and social scores in the medical outcomes of the Short-Form 36-item (SF-36) questionnaire, better strength and improved upper extremity skills in subscales of the Stroke Impact Scale (SIS) and in quality of life (QOL) [20, 21].

To our knowledge, no study has yet investigated the effects of home-based PA incentive programs outside of standard and structured therapy during the subacute phase of stroke recovery. The investigated home-based PA incentive program (Ticaa´dom) could be a useful strategy to increase daily PA, to change sedentary lifestyle over time, and to establish PA monitoring after stroke. The primary aim of this planned study is to evaluate how a 6MWT is affected by the Ticaa´dom program over 12 months in the subacute phase of stroke recovery. We hypothesize that the PA incentive program will increase daily PA and independence among stroke patients. The secondary objective is to evaluate whether and how well patients keep practicing PA at 6 months after the end of the PA incentive program.

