### Control group

The CG will receive traditional follow up, including a medical appointment at 1 and 6 months after the hospital discharge. The CG will not monitor their PA and will not receive home visits or telephone calls. After inclusion, the PA therapist will give an explanation of PA recommendations and the benefits of an active lifestyle on stroke recurrence prevention.

The Ticaa’dom protocol is a strategy to monitor and incite PA at home in stroke survivors. In this context, ambulatory care in stroke rehabilitation – i.e. physiotherapy – will be authorized during the trial for both groups. In contrast, intensive after-discharge rehabilitation programs conducted by the hospital’s rehabilitation service or participation in other PA programs will not be allowed during the experiment. If hospital rehabilitation is mandatory, the participant will be excluded from the study.

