## Discussion

The aim of the proposed study is to evaluate how a 6-month home-based physical activity incentive and education program affects functional capacity during the subacute phase of stroke recovery. The primary objective of the intervention is to encourage patients to meet PA recommendations and increase their 6MWT distance. The study is therefore designed to determine whether the home-based PA incentive program induces lifestyle changes and increases the amount of PA at medium-term and long-term follow up.

A previous study demonstrated that a home-based education program significantly reduced systolic blood pressure and body mass index, while it improved the distance the patient could walk after 12-month follow up [32]. However, the studied population included patients with transient ischemic attack, and their walking capacity and PA were measured subjectively (deliberate exercise walks). Therefore, to avoid these biases, our proposed study will only include stroke patients, and the protocol will provide objectively measured PA using a body-monitoring device.

Another previous randomized controlled trial showed that a home-based PA program had positive effects on the following: functional capacity, Barthel Index, physical and mental scores in the SF-36 questionnaire, and reduced risk of fracture after 12-month follow up [33]. Furthermore, a randomized controlled trial in a small sample of hemiplegic patients demonstrated that a home-based PA program was feasible, safe, and led to improved 6MWT distance and Timed Up-And-Go (TUG) test time [34]. Additional evidence is required on home-based PA in the subacute phase of stroke recovery.

The main limitation of the study will be the absence of PA monitoring in the control group. However, PA monitoring in the CG could bring about other forms of bias, such as the Hawthorne effect [35], i.e. the presence of a sensor could cause patients to change their lifestyles. Additionally, adherence to PA monitoring is reportedly low in stroke populations with low levels of balance, self-efficacy and walking endurance [36]. Despite this, remote PA monitoring is a common method used to quantify physical activity [14, 37]. Half of the studies in stroke patients have used accelerometers to measure walking or gait skills, and a third of them have used accelerometers to assess upper limb or arm movement [12].

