Our home-based PA incentive program will not impose a standard or specific PA protocol. Incentive will be based on post-stroke PA recommendations and monitoring using a physical activity sensor (daytime), home visits (every 3 weeks), and telephones calls (every week). We will supervise the PA monitoring using this method during the PA incentive period (6 months). Overall, it is expected that the study will provide evidence on the benefits of the Ticaa’dom program in the subacute phase of stroke recovery. We hypothesize that the intervention will lead to improvements in physical, psychological, and sociological aspects related to daily PA.

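### The tests named for change across T0, T1 and T2 are within-arm, and armband activity data are planned only in HB-PAI during months 0–6, so the Discussion's claim on longer-term physical activity needs a between-arm contrast and narrower wording

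*Protocol article*

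**What the plan says.** All references are to the protocol article.

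**Tests.** Statistical analysis names three sets of comparisons and one optional model:
- For the primary outcome: "The analysts will compare the 6MWT distance between each group using either the matched" Student's *t* test or Mann–Whitney.
- For other quantitative variables: "We will compare the distributions of quantitative variables using" Student's *t* test or Mann–Whitney.
- For change over the three visits: "They will also compare data between T0, T1 and T2 in both groups using the Friedman test and Wilcoxon matched pairs test".
- Optionally: "Multivariate linear regression analysis may be performed, taking prognostic factors into account".

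Only the third item mentions T0, T1 and T2.

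**Aims on PA.** The secondary objective in Background is to "evaluate whether and how well patients keep practicing PA at 6 months after the end of the PA incentive program". The Discussion says the study is designed to "determine whether the home-based PA incentive program induces lifestyle changes and increases the amount of PA at medium-term and long-term follow up".

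**PA measurement.** The armband belongs to the incentive phase (Intervention). On its duration, the Discussion says: "We will supervise the PA monitoring using this method during the PA incentive period (6 months"). After that, HB-PAI has six months of traditional follow up (Study design and settings). For controls: "The CG will not monitor their PA and will not receive home visits or telephone calls". The other PA measure is the MAQ, a self-report covering the previous six months (Outcomes). The Discussion names the lack of monitoring in the control group as the study's main limitation.

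**The concern.** Patients enter within 6 months of stroke (Participants), so walking distance, independence and activity may all change between T0 and T2 without any programme. A Friedman or Wilcoxon test inside one arm measures that change together with any programme effect. Setting a significant result in one arm beside a non-significant result in the other does not test the difference between arms.

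The PA claim has a second difficulty. The Discussion attributes medium-term and long-term activity to the programme, but the only objective instrument is worn by one arm and is taken off when the programme ends. At stake is whether the statements on change and on maintained activity will be randomized comparisons or before-after descriptions presented as programme effects.

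**Working it through.** The article gives no figure for these analyses, so there is none to reproduce. The check has two parts.

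**1. Which PA comparisons the design allows**

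| Period | HB-PAI armband | Control armband | MAQ, both arms |
|---|---|---|---|
| Months 0–6 | yes (Intervention; Discussion) | no (Control group) | at T1, recall covers months 0–6 |
| Months 6–12 | none described (traditional follow up) | no | at T2, recall covers months 6–12 |

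The MAQ column assumes collection at T1 and T2 in both arms. Outcomes sets assessments at T0, T1 and T2 without limiting them to one arm, but the outcome list and schedule are in Figs. 2 and 3, which are not shown. No row holds armband data from both arms, and the second row, which is the period of the secondary objective, holds none. The Discussion acknowledges the control-arm gap but not the gap in months 6–12.

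**2. How within-arm tests behave when the programme does nothing**

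Inputs: 36 per arm (the required number in Sample size calculation, before the addition of 15%: 36 × 1.15 = 41.4, hence 42); two-sided 5% level; the same true mean change in both arms. The article gives no value for that change, so it is assumed over a range from 0 to 1.0, in units of the standard deviation of change. Each setting has 4,000 simulated trials, with a Wilcoxon test in each arm and a Mann–Whitney test between arms on the change.

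If each arm is independently significant with probability *p*, then P(HB-PAI significant, control not) = *p*(1 − *p*), which cannot exceed 0.25.

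| Common change (SD) | HB-PAI significant within-arm, *p* | *p*(1 − *p*) | HB-PAI alone, simulated | Between-arm test of change |
|---|---|---|---|---|
| 0 | 4.1% | 3.9% | 3.8% | 4.9% |
| 0.2 | 20.8% | 16.5% | 16.6% | 5.1% |
| 0.3 | 40.4% | 24.1% | 24.2% | 4.7% |
| 0.4 | 63.2% | 23.3% | 23.4% | 4.8% |
| 0.5 | 81.7% | 15.0% | 14.4% | 4.9% |
| 0.7 | 98.4% | 1.6% | 1.8% | 5.5% |
| 1.0 | 100% | 0% | 0.03% | 4.5% |

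Worked row, 0.3 SD: 0.404 × (1 − 0.404) = 0.241.

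HB-PAI alone is significant most often at a modest common change and hardly ever when the change is nil or large. The second column matters as well: read by itself, a significant change in HB-PAI becomes near certain as spontaneous recovery grows, with no programme effect at all. The between-arm test stays near 5% throughout, counting both directions.

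**The case against.** The opposing case is substantial, and much of it stands.

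- *The secondary objective might be read as assigned to the within-arm tests.* It is not. Statistical analysis ties it to no test, and the general Student or Mann–Whitney comparison of quantitative variables can cover the MAQ. A comparison of randomized arms at T2 is controlled and needs no change model.
- *It might be inferred that no PA finding could be attributed to the programme.* That goes too far. A randomized comparison of self-reported PA appears available; what is missing is a randomized comparison of objective PA.
- *The Discussion might be read as promising an objective between-arm PA effect.* The aim on medium-term and long-term activity and the remark on objective measurement stand in separate paragraphs, and the remark is true of HB-PAI. No sentence promises objective PA at T2.
- *Friedman might be thought to lose every patient with a missed visit.* Interruption and exclusion conditions excludes absentees and sets last observation carried forward, so under the written rules the test would add little or no loss.
- *The simulation models a decision rule that the article never states.* Correct. It shows what the named tests can and cannot support; it is not a forecast of the trial's error rate.
- *As worded, the objective is partly descriptive:* only HB-PAI patients had a programme to keep up. A within-arm description answers that question legitimately, but not the Discussion's aim of showing what the programme induces.
- *Modelling detail belongs in the statistical analysis plan.* In general yes, and the article says one will be written. But here the article itself names the tests for change, and no analysis plan can supply armband data that were not collected.

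**Conclusion.** The point holds in a limited form. The only tests tied to T0, T1 and T2 are within-arm and cannot separate a programme effect from recovery. The between-arm tests name no time point, change score or baseline adjustment, and regression is optional. Objective PA cannot be compared between arms at any time, and none appears planned for anyone in months 6–12. The Discussion states its longer-term PA aim without narrowing it to what can be compared.

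On size: with equal true change in both arms, HB-PAI alone is significant within-arm in 0% to about 24% of trials, against about 5% for a between-arm test of change. This rests on 36 per arm, normally distributed change and an assumed size of common change; where in the range this trial would fall is unknown. The statement on months 6–12 is inferred from the text, because the schedule figures are not shown.

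**What to change.** 1. **Change and maintenance.** Base these claims on between-arm contrasts with 95% confidence intervals: the difference at T1 and at T2, each adjusted for T0, and the difference in change from T1 to T2. One model with group, visit and their interaction gives all three. Read the last contrast beside the T2 difference: a value near zero fits either a gain that was kept or a gain that never arose.
2. **Within-arm results.** Report them descriptively, and do not use Friedman or Wilcoxon p-values as evidence for the programme.
3. **PA endpoint.** Name the MAQ in both arms as the endpoint for the PA claims, after confirming from the schedule that it is taken at T0, T1 and T2. Its six-month recall at T0 reaches back before the stroke, given entry within 6 months of it. The T0 score is therefore usable as a covariate but is not a measure of activity at discharge.
4. **Armband data.** Use them only to describe HB-PAI in months 0–6.
5. **Discussion.** Reword the aim so that the between-arm PA claim concerns self-reported PA, and add the months 6–12 gap to the stated limitation.

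The cost is wording in the analysis plan and a narrower claim, with no new data if the MAQ schedule is as assumed. Trial status reports 50 of 84 patients enrolled, so recruitment was still open when the article was written. The downside is that the PA conclusion will rest on recall by patients who know their allocation, and this should be stated with the result.
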